**Prevalence and relative severity of the outcome**

Initial assessment of severity of outcome will be done by the study team, but Patient and Public Involvement (PPI) input on this will be vital to ensure that their priorities feed into an understanding of which outcomes are most important to women with lived experience of patient decision making around medication use in pregnancy. The magnitude of the estimated increased risk of the outcome together with the prevalence of the outcome will be summarised as population attributable risks (i.e., the proportion of cases of the relevant adverse outcome that would be attributed to the use of the given drug in pregnancy if the association were causal).

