### Objective 2: Signal detection

Adverse outcomes will be defined as above. Exposures will be prescriptions of individual active ingredients of medications. The estimated dates of pregnancy will be used to identify any medications prescribed in the three months prior to pregnancy or during pregnancy, and analyses will be run for each trimester separately as well as for the three-month period prior to pregnancy.

We will apply standard Bayesian signal detection models using the Information Component (IC) [24–26]. This method is based on comparing the frequency of occurrence of the outcome of interest in mothers prescribed the medication of interest compared to the frequency of occurrence of the outcome of interest in mothers not prescribed the medication of interest for each medication/outcome pair. IC values that are positive indicate that the outcome and prescribed medication occur more frequently together than would be expected due to chance if both events were independent. In brief the observed counts (a,b,c,d from a two-by-two table) are assumed to have a Multinomial distribution (pa,pb,pc,pd,n). With a Dirichlet prior distribution for pa pb pc and pd the corresponding posterior distribution is also a Dirichlet distribution. Assuming an uninformative prior likelihood, 100,000 random samples from the proposed posterior Dirichlet distribution can be generated and the median IC with its 95% credible intervals obtained [27]. Pairs with a positive lower 95% credible interval have sufficient evidence that they are occurring more frequently than would be expected due to chance and are classified as signals.

Our new method of hierarchical modelling will then use these results to identify groups in the data using bi-clustering techniques. For this method, pairs with a positive lower 90% credible interval using the IC are considered ‘potential signals’. A group is defined as containing all medication/outcome pairs where all medications in the group have a potential signal with the same outcomes in the group. Medications with similar pharmacological properties are likely to be in the same groups, but the actual group membership is determined purely by the data. These groups will then be used to calculate an observed to expected ratio, adjusted for groupings, for each medication/outcome pair.

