**Prevalence of use overall and in under-represented groups**

Commonly prescribed medications will be given priority over those prescribed more infrequently. We will also be able to identify any medications prescribed more frequently in under-represented socio-demographic groups from our results in objective 1, which will be an additional priority criterion.

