**Availability of alternative medications with known safety**

The potential for change in prescribing practice is greater for medications where there are alternative medications that can be prescribed for any given indication. In cases where there are not known safe alternatives the risks of not taking a given medication will be an important consideration.

Initial collation of information gathered from the above 5 domains will be done by the study team and formatted in an appropriate way for an initial PPI workshop. Output from this workshop will be added to the information from the initial 5 domains and taken to the Study Advisory Board Workshop. The multidisciplinary team will review information from the 5 domains and PPI discussions prior to the workshop and during the workshop will have small group and whole group discussions through which a prioritised list of medications will be generated.

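### The attributable-risk summary is said to combine effect size with outcome prevalence, but the proportion it defines does not carry outcome prevalence

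*Protocol article*

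**What the plan says.** Objective 3 of the protocol article collects information in five domains to decide which medications need further study. One domain is headed "Prevalence and relative severity of the outcome". Severity is to be judged by the study team with patient and public input. The quantitative part is one sentence: "The magnitude of the estimated increased risk of the outcome together with the prevalence of the outcome will be summarised as population attributable risks". A parenthesis in the same sentence explains the term as "the proportion of cases of the relevant adverse outcome that would be attributed to the use of the given drug in pregnancy", supposing the association to be causal.

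The preceding domain deals with how often a medicine is used: "Commonly prescribed medications will be given priority over those prescribed more infrequently".

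The last domain's section describes how the material is used. The study team collates the five domains, a patient and public workshop adds its output, and the advisory board workshop then holds small-group and "whole group discussions through which a prioritised list of medications will be generated".

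**The concern.** The sentence assigns the metric a task and then defines it so that it cannot do that task. Effect size and outcome prevalence are meant to be brought together. A proportion of cases, however, has the total number of cases as its denominator, so the outcome's frequency divides out. What remains is the relative effect and the frequency of exposure.

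Workshop members who are told that the figure combines risk with outcome prevalence could read equal values as equal burden, when the numbers of affected pregnancies differ a hundredfold or more. The figure feeds the choice of three signals for the Objective 4 cohort studies and the longer list of medications for further research, which the Discussion names as a strength. Frequency of prescribing would inform two domains, while outcome frequency would have no named numerical summary.

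**Working it through.** The article gives no numerical attributable risk, so there is no figure to reproduce. The check is of the definition.

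**Inputs.** Exposure prevalence p, risk ratio RR (prescribed versus not prescribed) and the risk in the unexposed p0. The article states none of these; every value below is an assumption for illustration.

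**Step 1: the defined quantity.**
- Overall outcome risk: P(D) = p·RR·p0 + (1 − p)·p0 = p0·[1 + p(RR − 1)].
- Proportion of cases attributable: [P(D) − p0]/P(D) = p(RR − 1)/[1 + p(RR − 1)]. The term p0 cancels.

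**Step 2: the absolute counterparts.**
- Excess cases per pregnancy in the population: P(D) − p0 = fraction × P(D).
- Excess cases per exposed pregnancy: p0(RR − 1), with p0 = P(D)/[1 + p(RR − 1)].

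**Step 3: numbers, p = 2% and RR = 2.** The fraction is 0.02/1.02 = 1.96%.

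| Outcome prevalence P(D) | Fraction | Excess per 100,000 pregnancies | Excess per 1,000 exposed |
|---|---|---|---|
| 0.1% | 1.96% | 1.96 | 0.98 |
| 1% | 1.96% | 19.6 | 9.8 |
| 10% | 1.96% | 196 | 98 |

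**Step 4: range of inputs.** With p0 running from 0.01% to 10%, the fraction stays fixed in each row while excess cases rise 1,000-fold.

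| p | RR | Fraction at every p0 | Excess per 100,000, p0 = 0.01% to 10% |
|---|---|---|---|
| 1% | 1.5 | 0.50% | 0.05 to 50 |
| 1% | 2 | 0.99% | 0.1 to 100 |
| 5% | 1.5 | 2.44% | 0.25 to 250 |
| 5% | 2 | 4.76% | 0.5 to 500 |
| 10% | 1.5 | 4.76% | 0.5 to 500 |
| 10% | 2 | 9.09% | 1 to 1,000 |

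**Step 5: does another effect scale rescue the definition?** The cancellation is exact on the risk-ratio scale. At p = 5%:
- With the odds ratio held at 2, the fraction falls from 4.76% at p0 = 0.01% to 3.93% at p0 = 10%.
- With the risk difference held at 0.1%, it falls from 33.3% to 0.05% over the same range.

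On neither scale does a commoner outcome receive a higher value; the movement is opposite to the stated intent.

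**The case against.** **No ranking formula exists.** A reader might infer that rare and common harms will rank the same, or that the workshops choose from this number alone. The article supports neither. The list comes from discussion of five domains plus patient and public input, with no weights or scores, and severity is assessed separately. For the same reason prescribing frequency is not counted twice in any arithmetical sense; priority for common medicines is a deliberate choice. This stands, and it limits the consequence.

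**Observed/expected in place of the risk ratio.** Objective 2 says "These groups will then be used to calculate an observed to expected ratio, adjusted for groupings, for each medication/outcome pair", and a reader might infer that this ratio will be put into the attributable-fraction formula. The article does not say so, and the two-by-two counts give a risk ratio directly. At 2% exposed and RR 2, the substitution would in any case change little: observed/expected is 2/1.02 = 1.96, and the fraction 1.89% instead of 1.96%. This is not part of the point.

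**Terminology.** Population attributable risk is also used for the absolute excess, which does depend on outcome prevalence. The article's own parenthesis rules out that reading here.

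**Condensed article.** Workshop material may well show outcome prevalence too, and an article need not list every column. That would answer a complaint of omission. It does not answer a stated definition that conflicts with the purpose given in the same sentence.

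**Over-precision.** Signal-stage associations are unadjusted, so excess-case counts could suggest more certainty than they deserve. This is fair and is met by labelling and credible intervals; the fraction has the same weakness.

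**Conclusion.** The point holds as an error of definition. At a given risk ratio and exposure prevalence, the defined proportion is the same for any outcome prevalence: 1.96% at both 0.1% and 10% with 2% exposed and RR 2, against about 2 and 196 excess cases per 100,000 pregnancies. The sizes rest on assumed inputs; the cancellation does not. No other numerical summary carrying outcome prevalence is named for this domain.

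The consequence is moderate. The metric can mislead one of five inputs to a deliberative process. It does not determine the list, and it affects no signal threshold and no effect estimate in the Objective 4 cohort studies. The correction is still worth making because the stated purpose is sound and the present definition does not serve it.

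**What to change.** Rewrite the sentence so that the metric is attributable (excess) cases per 100,000 pregnancies, that is, the attributable fraction multiplied by outcome prevalence. Ideally add excess cases per 1,000 exposed pregnancies.

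Both follow from the Dirichlet draws already planned under Objective 2. Take a and b as prescribed with and without the outcome, and c and d as not prescribed with and without it (the article does not label the cells). For each draw:
- risk if prescribed: R1 = pa/(pa + pb)
- risk if not prescribed: R0 = pc/(pc + pd)
- excess per 1,000 exposed: 1,000 × (R1 − R0)
- excess per 100,000 pregnancies: 100,000 × (pa + pc − R0)

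Report medians with credible intervals, and label them as unadjusted signal-stage figures that would be attributable only if the association were causal. The fraction may stay as a secondary column under its own name, with the outcome prevalence beside it.

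The minimum repair is to keep the fraction, stop describing it as including outcome prevalence, and show that prevalence next to it.

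The cost is one paragraph and a few lines of code, with no new data. By the Timeline, signal detection results are expected by autumn 2026 and prioritisation by spring 2027, so the change can be made before the workshop material is prepared.

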**Availability of alternative medications with known safety**

The potential for change in prescribing practice is greater for medications where there are alternative medications that can be prescribed for any given indication. In cases where there are not known safe alternatives the risks of not taking a given medication will be an important consideration.

Initial collation of information gathered from the above 5 domains will be done by the study team and formatted in an appropriate way for an initial PPI workshop. Output from this workshop will be added to the information from the initial 5 domains and taken to the Study Advisory Board Workshop. The multidisciplinary team will review information from the 5 domains and PPI discussions prior to the workshop and during the workshop will have small group and whole group discussions through which a prioritised list of medications will be generated.

### Objective 4: Retrospective cohort studies for identified signals

Retrospective cohort studies of three prioritised medication signals will be done, to quantify associations with adverse outcomes while adjusting for confounding. Details of the analysis plan will be determined by the specific drug and outcome being investigated.

### Timeline

There is no data collection for this project; data have already been extracted centrally by CPRD from routinely collected data. Record screening will be completed by June 2026. We anticipate generating results for objective 1 (descriptive analysis) by summer 2026; objective 2 (signal detection) by autumn 2026; objective 3 (prioritisation process) by spring 2027; and objective 4 (retrospective analyses) by summer 2027.

## Discussion

### Strengths

This study leverages contemporary large-scale, population-based electronic health records from national primary care databases, enabling assessment of prescribing during pregnancy across England. The use of validated pregnancy registers and established linkages to hospital admissions, mortality records, and socio-economic data strengthens outcome ascertainment and allows assessment of maternal as well as fetal and infant health.

A major strength is the systematic signal detection approach applied across all medications and a wide range of outcomes, rather than restricting analyses to pre-specified drug–outcome pairs. The use of advanced Bayesian and hierarchical methods allows information sharing across related medications and outcomes, improving the ability to detect potential safety signals, including for less commonly prescribed medicines.

The study team are a multi-disciplinary group with expertise in epidemiology, statistics, primary care, obstetrics, paediatrics, clinical pharmacology and lived experience of prescribing in pregnancy.

The integration of the quantitative findings with existing evidence and structured patient and expert input will enhance the relevance and transparency of the prioritisation process, and the prioritisation process will produce a valuable list of medications requiring further research in addition to the three that we will be able to investigate in this study.

### Limitations

As an observational study based on routinely collected data, there is potential for misclassification of exposures, outcomes, and of pregnancy status. The CPRD pregnancy register is based on an algorithm that searches for clinical codes likely to indicate pregnancy and generates estimated gestational dates from this. Some of the clinical codes used may generate false pregnancies, as has been highlighted in analyses of valproate use where the use of codes such as ‘*Advice on risk harm to fetus from maternl medictn dur preg’* are used when a patient is not pregnant [28]. To minimise the impact of this, where a pregnancy is based on a single code, the appropriateness of including these pregnancies will be reviewed based on the original codes used. Where HES linkage is available, we will also use this to triangulate whether a pregnancy is a true pregnancy, pregnancy outcome, and estimated gestation dates [17].

There is also the potential for residual confounding, particularly confounding by indication, which may not be possible to fully address through statistical adjustment. Prescription records indicate medications issued in primary care but we do not have data on whether prescriptions were collected and taken, so exposure misclassification must be considered.

Outcome misclassification is also possible due to imperfect coding, variation in recording practices, and limited clinical detail for some outcomes. Although signal detection methods are designed for hypothesis generation rather than causal inference, there remains a risk of identifying spurious associations arising from multiple testing or correlated exposures and outcomes. For these reasons, signals identified in this study will be interpreted cautiously and used primarily to prioritise medications for further investigation rather than to draw any definitive conclusions about causality.

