**Fig 1 pone.0349045.g001:**
[figure not shown]
Study population and data sources for exposures and outcomes.

We will use data from the CPRD pregnancy register to identify pregnancy episodes and estimated delivery dates and the Mother-Baby link to identify infant outcomes [15,16]. CPRD contains data contributed by GP practices using Vision (Gold) and EMIS (Aurum) clinical systems. The CPRD pregnancy register has been validated against linked HES and the ONS live birth data [15]. Data will be linked to HES data, ONS death registration data, and IMD data.

The study protocol was approved by CPRD’s Research Data Governance group (Ref: 24_004518). Based on these approvals individual patient consent was not required.

Analyses will be conducted within CPRD Safe (trusted research environment).

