### Study population

The study will include women in the CPRD pregnancy register who have been registered for at least six months before the start of each pregnancy to ensure sufficient recording of long-term health conditions. An individual woman can contribute more than one pregnancy. The CPRD pregnancy register uses an algorithm based on primary care records to generate information on likely pregnancies, dates, and outcomes. This pregnancy register has been validated and can be supplemented with hospital admissions data to further improve accuracy of information on pregnancy dates and outcomes [15,17,18].

Non-singleton pregnancies will be excluded. Mother and baby will be followed up for up to one year after birth to look at maternal post-partum and infant outcomes.

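### The code review for false pregnancies is triggered by the number of codes, although the hazard the protocol names is a type of code

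*Protocol article*

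**What the plan says.** The Limitations section of the protocol article states the hazard plainly: "Some of the clinical codes used may generate false pregnancies, as has been highlighted in analyses of valproate use". Its example is a code for advice about harm to the fetus from maternal medication, used for patients who are not pregnant.

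Two safeguards follow.

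- **Code review:** "where a pregnancy is based on a single code, the appropriateness of including these pregnancies will be reviewed based on the original codes used".
- **Hospital records:** "Where HES linkage is available, we will also use this to triangulate whether a pregnancy is a true pregnancy, pregnancy outcome, and estimated gestation dates".

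The Study population section adds that the pregnancy register "can be supplemented with hospital admissions data to further improve accuracy of information on pregnancy dates and outcomes", and the Data source section says "Data will be linked to HES data, ONS death registration data, and IMD data".

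The retained episodes feed two analyses. Objective 1 reports prescribing rates per 1000 pregnancies. Objective 2 compares "the frequency of occurrence of the outcome of interest in mothers prescribed the medication of interest" with the frequency in mothers not prescribed it, and declares a signal when the lower 95% credible limit of the Information Component (IC) is positive.

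**The concern.** The hazard is defined by meaning and the review by number. Two entries of advice about a medicine are no better evidence of pregnancy than one, yet a second entry can take the episode outside the review. The trigger therefore misses part of the problem it was written for.

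The error is also linked to exposure. Advice of this kind is recorded because of the medicine, so a resulting false episode is likely to be counted as exposed to that medicine if a prescription falls in the exposure window. A false episode cannot contribute a congenital anomaly, a premature delivery or a stillbirth. If it sits in the denominator for such an outcome, it lowers the observed/expected ratio for that medicine, and a true association could miss the signal limit. The Limitations section warns of spurious associations from the screen but does not mention signals lost in this way. The same episodes would overstate prescribing in pregnancy under Objective 1, and prevalence of use is one of the prioritisation criteria in Objective 3.

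**Working it through.** **Reading the text.** What the two safeguards cover:

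| Episode rests on | Code review | Hospital-record check |
|---|---|---|
| One advice code | Yes | Where linked |
| The same advice code twice | Only if a single code means one distinct code | Where linked |
| Two different advice or counselling codes | No | Where linked |

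The last row is missed on either reading of the trigger. The middle row depends on the reading, which the article does not settle.

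**Inputs.** The documents give no figure for false pregnancies, so there is none to reproduce. All of these are assumptions:

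- f, the share of counted exposed pregnancies still false after both checks: 0 to 30%.
- E0, the expected cases among the truly exposed: 20.
- True observed/expected ratio RR: 2.0 or 1.5.
- False episodes have no outcome and are in the denominator.

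**Step 1: ratio.** The counted exposed number is the true number divided by (1-f), so the expected count becomes E0/(1-f) while the observed count is unchanged:

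observed ratio = RR × E0 / [E0/(1-f)] = RR × (1-f)

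**Step 2: chance of a signal.** Take O ~ Poisson(RR × E0) and declare a signal when the 2.5% quantile of Gamma(O + 0.5) exceeds E0/(1-f). This is a simple stand-in for the IC rule.

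| f | Expected count | Smallest O that signals | Ratio if RR 2.0 | Chance of signal | Ratio if RR 1.5 | Chance of signal |
|---|---|---|---|---|---|---|
| 0 | 20.0 | 30 | 2.0 | 96% | 1.5 | 52% |
| 10% | 22.2 | 32 | 1.8 | 91% | 1.35 | 38% |
| 20% | 25.0 | 36 | 1.6 | 76% | 1.20 | 16% |
| 30% | 28.6 | 40 | 1.4 | 52% | 1.05 | 5% |

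**Step 3: the protocol's own statistic.** Using 100,000 Dirichlet draws with a flat prior, IC = log2[pa/((pa+pb)(pa+pc))], 1,000,000 pregnancies in total and a 2% baseline risk (also assumed), and the observed count set at its expected value:

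| Truly exposed | RR | f | IC (95% interval) | Signal |
|---|---|---|---|---|
| 1,000 | 2.0 | 0 | 1.02 (0.56 to 1.43) | yes |
| 1,000 | 2.0 | 30% | 0.51 (0.05 to 0.92) | yes, barely |
| 1,000 | 1.5 | 0 | 0.61 (0.08 to 1.09) | yes |
| 1,000 | 1.5 | 10% | 0.46 (-0.07 to 0.93) | no |
| 500 | 2.0 | 20% | 0.72 (0.06 to 1.29) | yes, barely |
| 500 | 2.0 | 30% | 0.53 (-0.13 to 1.10) | no |
| 3,000 | 2.0 | 30% | 0.49 (0.23 to 0.74) | yes |

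The direction and scale agree with Step 2. Less common medicines and modest effects are the vulnerable ones.

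**Step 4: Objective 1.** The count of pregnancies prescribed the medicine is inflated by 1/(1-f): 1/0.9 = 1.11, 1/0.8 = 1.25 and 1/0.7 = 1.43, that is by 11%, 25% and 43%. The rate per 1000 rises by nearly as much when false episodes are a small part of all pregnancies.

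**The case against.** The case against has real weight.

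- **The single-code review is not the only safeguard.** The hospital-record check does not depend on how many codes there are, and linkage is planned. This stands. What is left is multi-code episodes without linkage, or linked episodes that the hospital record does not confirm. Absence of a hospital record cannot by itself separate a false pregnancy from an early loss managed elsewhere.
- **A single code may mean one distinct code.** Repeats of the same code would then be reviewed. This narrows the gap but leaves two different advice codes outside it.
- **Repeat coding is not shown.** No section says how often advice codes recur within an episode, and nothing supports any particular f. This stands, and it makes every figure above an illustration.
- **False episodes are not free of all outcomes.** Depression, infection and stroke are among the listed maternal outcomes and can be recorded in a woman who is not pregnant. The (1-f) factor does not apply to them.
- **The denominator is not fixed.** Infant outcomes come through the Mother-Baby link. If those tables are restricted to linked births, false episodes never enter them and nothing is diluted.
- **Exposure is not automatic.** An advice code does not make an episode exposed in every window. Medicines with known warnings may also be annotated as having a known harmful effect, so a weakened signal there matters less.
- **An article condenses.** How unconfirmed episodes are resolved may well be in the full protocol. That silence is not criticised here; the point is the trigger the article does state.

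**Conclusion.** The point holds in limited form. The stated trigger does not match the stated hazard: episodes supported by two or more advice-type codes are not caught by the code review and rely on hospital triangulation where linkage exists. Any that survive both checks bias the ratio downwards by about (1-f) for outcomes that need a true pregnancy, where those episodes are in the denominator, and inflate the Objective 1 rates.

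The size is unknown. The fall from 96% to 52% at f = 30% rests on an assumed f, 20 expected cases and a ratio of 2.0; with 3,000 exposed at 2% baseline risk the same f leaves the signal standing.

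A reader might infer that repeated advice codes escape all scrutiny, that the added episodes are free of every outcome, or that true harms will be missed. The documents support none of these: there is a second check independent of code count, several maternal outcomes need no pregnancy, and neither the frequency of repeat coding nor f is given. This is a weakness in a stated rule that is cheap to mend, not a demonstrated error in the results.

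**What to change.** Define the review by code content. Any episode whose supporting codes are all medication-advice, counselling or similarly non-specific codes, however many, goes to review, with priority to those without hospital confirmation. This also removes the ambiguity over what a single code means.

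Run the signal screen and the Objective 1 rates with and without uncorroborated episodes, and report the share affected for each medicine, which gives an upper guide to f. Keep this as a sensitivity analysis. Requiring corroboration as a primary exclusion would be a debatable trade, because it would drop true early losses that left no other record.

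The cost is a short code list and one rerun on data already extracted, best settled before signal detection begins. The downside is that some true early losses with no other record are left out of the restricted run; comparing the two runs shows how much the results depend on these episodes.
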